## Abstract

**Background:**

Type 2 diabetes mellitus (T2DM) and coronary heart disease (CHD) are two chronic diseases that cause a tremendous burden. To reduce this burden, several programmes for optimising the care for these diseases have been developed. In Germany, so-called disease management programmes (DMPs), which combine components of Disease Management and the Chronic Care Model, are applied. These DMPs have proven effective. Nevertheless, there are opportunities for improvement. Current DMPs rarely address self-management of the disease, make no use of peer support, and provide no special assistance for persons with low health literacy and/or low patient activation. The study protocol presented here is for the evaluation of a programme that addresses these possible shortcomings and can be combined with current German DMPs for T2DM and CHD. This programme consists of four components:
Meetings of peer support groupsPersonalised telephone-based health coaching for patients with low literacy and/or low patient activationPersonalised patient feedbackA browser-based web portal

**Methods:**

Study participants will be adults enrolled in a DMP for T2DM and/or CHD and living in North Rhine-Westphalia, a state of the Federal Republic of Germany. Study participants will be recruited with the assistance of their general practitioners by the end of June 2021. Evaluation will be performed as a pragmatic randomised controlled trial with one intervention group and one waiting control group. The intervention group will receive the intervention for 18 months. During this time, the waiting control group will continue with usual care and the usual measures of their DMPs. After 18 months, the waiting control group will also receive a shortened intervention. The primary outcome is number of hospital days. In addition, the effects on self-reported health-state, physical activity, nutrition, and eight different psychological variables will be investigated. Differences between values at month 18 and at the beginning will be compared to judge the effectiveness of the intervention.

**Discussion:**

If the intervention proves effective, it may be included into the DMPs for T2DM and CHD.

**Trial registration:**

The study was registered in the German Clinical Trials Registry (Deutsches Register Klinischer Studien (DRKS)) in early 2019 under the number 00020592. This registry has been affiliated with the WHO Clinical Trials Network (https://www.drks.de/drks_web/setLocale_EN.do) since 2008. It is based on the WHO template, but contains some additional categories for which information has to be given (https://www.drks.de/drks_web/navigate.do?navigationId=entryfields&messageDE=Beschreibung%20der%20Eingabefelder&messageEN=Description%20of%20entry%20fields ). A release and subsequent number assignment only take place when information for all categories has been given.

**Supplementary Information:**

The online version contains supplementary material available at 10.1186/s13063-021-05636-4.

## Administrative information

**Table Taba:** 

Title {1}	A Pragmatic Randomised Controlled Trial referring to a Personalised Self-management SUPport Programme (P-SUP) for persons enrolled in a disease management programme for type 2 diabetes mellitus and/or for coronary heart disease
Trial registration {2a and 2b}.	The study was registered in the DRKS at the beginning of 2019 under the number 00020592. Since October 2008 the DRKS has been maintained as a primary registry of the World Health Organization (WHO) and thus fulfils the requirements of the International Committee of Medical Journal Editors.
Protocol version {3}	P-SUP_Study Protocol_Version _03
Funding {4}	The development and evaluation of the intervention are fully funded by the Federal Joint Committee (Gemeinsamer Bundesausschuss (G-BA)). https://innovationsfonds.g-ba.de/projekte/neue-versorgungsformen/p-sup-personalisiertes-selbstmanagement-unterstuetzungsprogramm.285

## Introduction

### Background and rationale {6a}

#### Background

Type 2 diabetes mellitus (T2DM) and coronary heart disease (CHD) are both chronic diseases with a high impact on public health. Analyses based on data of the European Health Interview Survey show that, in 2014, 7.7% of the adult German population suffered from diabetes mellitus, in most cases T2DM [1], and 4.8% from CHD [2]. The worldwide prevalence of diabetes mellitus in adult persons was estimated to be 8.5% for 2014 [3]. In comparison, for 1980, this prevalence was only 4.7% [3]. This indicates an enormous increase of diabetes mellitus within the last decades. This dramatic rise is largely due to the rise in T2DM [3]. There are no valid estimates of the worldwide prevalence of CHD. However, cardiovascular diseases, which include CHD, are considered to have been the cause of 17.9 million worldwide deaths in 2016, which accounted for 31% of all worldwide deaths in that year [4]. Together, T2DM and cardiovascular disease including CHD are major causes of premature death, disability, productivity loss, and decrease in quality of life [5]. Accordingly, T2DM and CHD contribute substantially to the medical, social, and economic burden caused by non-communicable diseases, and this burden constitutes a major challenge for healthcare systems around the world [6].

The burden caused by diseases like T2DM and CHD has motivated the development of approaches for effective coping with chronic diseases. The two best-known approaches are Disease Management and the Chronic Care Model [7]. Disease Management aims to provide disease-specific, evidence-based, coordinated, and integrated care for chronic sufferers from a defined condition with the goal of improving outcomes and life expectancy and of containing costs through pro-active care. An integral part of Disease Management is patient education and the activation of patients to perform self-management. There is international evidence for the effectiveness of Disease Management for both T2DM and CHD [8]. The Chronic Care Model emerged through summarisation of the results of a review of previous effective approaches for chronic disease care [9]. This model recommends the combination of several components of health care with each other. These components are ‘effective team care and planned interactions; self-management support bolstered by more effective use of community resources; integrated decision support; and patient registries and other supportive information technology’ [10]. As in the case of Disease Management, the Chronic Care Model has also proven to be effective for T2DM and CHD [10].

Disease Management and the Chronic Care Model constitute the conceptual basis of Germany’s Disease Management Programmes (DMPs). In these programmes, recommendations provided by Disease Management for the interaction between physicians and patients are combined with recommendations provided by the Chronic Care Model for the design of those parts of the health system that are relevant for the treatment of T2DM and CHD. Special hallmarks of the German DMPs are that they are patient-centred and physician-based, and that they include all patients with a certain condition in a preventive approach rather than targeting a high-risk population. There is evidence that the German DMPs improve clinical outcomes, quality of life and survival [11, 12]. However, current DMPs contain almost no components that support self-management and, thereby, health-promoting lifestyle behaviour. The only structured support of self-management consists in patient education classes [13]. Neglecting self-management in this way could be fatal because certain kinds of lifestyle behaviour, especially healthy nutrition and regular physical activity, have very favourable effects in cases of T2DM and CHD. They improve physical fitness, glycaemic control, blood pressure control and quality of life in patients [14]. For this reason, the effectivity of DMPs could increase substantially if they are extended to include components for enhancing self-management.

One approach for enhancing self-management is peer support, i.e. support from persons suffering from the same disease. This kind of support has several advantages compared to support provided by professionals. It is non-hierarchical, combines the benefits of both receiving and giving social support, provides prolonged emotional support, and affords opportunity to share similar life experiences. There is, in fact, extensive empirical evidence for the effectiveness of peer support for various health conditions, across age groups, social status and settings [15–17]. In addition to this, peer support has a further important advantage: it costs less than support provided by professionals. DMPs could therefore benefit from the integration of peer support components.

Other factors that influence self-management are health literacy and patient activation. Health literacy is the ability to seek, access, understand and apply information regarding one’s own health condition [18]. Patient activation is a multidimensional construct consisting of the dimensions ‘belief’, ‘knowledge’ and ‘skills’. Belief refers to the patients’ belief that they have an important role to play in shaping the treatment of their medical conditions, knowledge stands for the patients’ knowledge of how to manage their medical conditions and skills refers to the patients’ skills and behavioural repertoire in terms of acting according to their belief and knowledge [19]. There is extensive empirical evidence that health-related behaviour and medical outcomes are positively influenced by health literacy [20, 21] and patient activation [22]. These findings are especially relevant for the design of health care in Germany, as empirical evidence indicates that more than 50% of the German population have low health literacy [23]. Altogether, these findings suggest that the effectivity of DMPs in Germany could increase if components that specifically address the needs of patients with low health literacy or low patient activation are added.

As physical activity and nutrition are essential components of care for T2DM and CHD, findings regarding interventions designed to affect these two kinds of behaviour in persons with these diseases are also relevant. Hardly any research regarding the effectiveness of interventions for changing nutritional behaviour exists. However, such research does exist for physical activity and this research mainly refers to T2DM. There are several evaluation studies regarding interventions for promoting physical activity in persons with T2DM and even several reviews of these evaluation studies. The authors of a recent review of reviews of such evaluation studies identified 18 reviews referring to 113 separate trials [24]. From the results of these reviews, the authors inferred that two intervention components in particular help to promote physical activity: (1) giving feedback and (2) helping to integrate physical activity into daily life.

#### Rationale

The intervention presented here aims at removing the insufficiencies elaborated above and at applying the lessons that can be learned from previous research. The complete intervention will consist of four components:
Virtual and/or real meetings of peer support groups (PSGs)Personalised telephone-based health coaching for patients with low literacy and/or low patient activationPersonalised patient feedbackA browser-based web portal

The PSGs will be groups of persons suffering from T2DM and/or CHD. These groups will be organised by persons also suffering from at least one of these diseases. The groups will meet weekly either virtually or in person. One major purpose of these groups will be to provide peer support with regard to self-management. To some extent, this support will consist in mutual exchange of advice on how health-promoting behaviour can be integrated into daily life. Personalised telephone-based health coaching will only be provided to participants with low health-literacy and/or low patient activation as assessed by means of a questionnaire. The purpose of this coaching will be to compensate for deficits that people with these characteristics have with regard to their self-management. Specifically, the telephone-based health coaching will aim at improving patients’ motivational and volitional control regarding integration of health-promoting forms of behaviour into their daily lives. The personalised patient feedback will consist in information about the patient’s current medical condition and is intended to aid individual adjustment of self-management. The browser-based web portal will offer information designed to help with self-management. In addition, this portal will contain modules designed to increase participants’ motivation regarding integration of health-promoting forms of behaviour into their daily lives.

## Objectives {7}

### Primary hypothesis

P-SUP reduces the number of hospital days.

### Secondary hypotheses

The secondary hypotheses are based on a theoretical frame that outlines how the effect of the intervention on number of hospital days is mediated. According to this frame, the mediating variables can be assigned to three different levels: (1) the physical level, which refers to the physical health state experienced by the study participants; (2) the behavioural level, which refers to the health-related behaviour performed by the study participants; and (3) the psychological level, which refers to the variables that reflect the way the study participants think and feel. If one adds the realm of health care provision, in which the intervention takes place, and the realm of health care utilisation, which includes hospital days, a five-level frame results (see Fig. 1). According to this theoretical frame, two causal pathways exist along which the intervention will affect the number of hospital days. The first pathway is a chain of causal effects from level to level. On the second pathway, the behavioural level is left out and replaced by a direct link from the psychological level to the physical level (see Fig. 1).

**Fig. 1 Fig1:**
[figure not shown]
Theoretical frame

In addition to the number of hospital days, the intervention will also be evaluated with regard to variables that are assumed to mediate the effect of the intervention on the number of hospital days. These variables are self-reported physical health, which is assigned to the physical level; self-reported physical activity and self-reported nutrition, which are both assigned to the behavioural level; and eight variables belonging to the psychological level. The eight psychological variables are:
Intention to perform physical activity to the extent recommended by the World Health Organisation [26]Perceived behavioural control with regard to physical activity of this extentIntention to perform at least five of the nine items of health-promoting nutritional behaviour described in the questionnairePerceived behavioural control with regard to performing health-promoting nutritional behaviour of this extentSelf-efficacy with regard to health-related self-management,LonelinessDepressionAnxiety

Five of the eight psychological variables (i.e. intention with regard to physical activity, perceived behavioural control with regard to physical activity, intention with regard to nutritional behaviour, perceived behavioural control with regard to nutritional behaviour and self-efficacy with regard to health-related self-management) are assumed to affect behaviour and, mediated by this, experienced physical health. The remaining three psychological variables (i.e. loneliness, depression and anxiety) are assumed to affect experienced physical health directly. It is assumed that all the variables just mentioned (i.e. experienced physical health, the two behavioural variables and the eight psychological variables) will be positively affected by the intervention. Correspondingly, it is assumed that 18 months after the start of P-SUP, persons participating in this intervention will score better values on these variables than persons not participating in the intervention.

## Trial design {8}

The trial will be a pragmatic randomised controlled trial with one intervention and one waiting control group. Participants of the control group will receive the P-SUP-programme later than participants of the intervention group. The trial is pragmatic in that it will be performed in the exact setting in which it is ultimately intended to be applied, and in that all resources used will be available if the intervention is ultimately integrated into usual care. The allocation ratio of intervention to control is 6:7 because the drop-out rate for the intervention group is expected to be 30% and, for the control group, 40%. The trial is a superiority study [27] in which the superiority of the intervention to the comparator is to be demonstrated.

## Methods: participants, interventions and outcomes

### Study setting {9}

The study will be conducted jointly by several collaborating institutions in Germany. These institutions are IGKE Cologne, AMED Aachen, IFAM Bonn, SAM Cologne, ifam Düsseldorf, IFAM Essen, KPPP Cologne, DSHS Psychology and DSHS Movement. IGKE Cologne, AMED Aachen, IFAM Bonn, SAM Cologne, ifam Düsseldorf and IFAM Essen will approach general practices and recruit general practitioners (GPs), who will, in turn, recruit eligible patients. A substantial part of the intervention will be performed digitally or via telephone. The remaining part will consist in meetings of PSGs. The first PSG meetings will be held virtually via video conference tools. If the COVID-19 pandemic allows, later meetings can be held in reality. These meetings will be held either outdoor or in rooms that will be specifically rented for the meetings and will usually not belong to institutions providing any kind of health care. The meetings will be organised by selected patients, i.e. the PSG leaders. In some of the meetings, sports therapists or other experts will support the PSG leaders.

### Eligibility criteria {10}

All general practices in the study region will be eligible as long as they are willing to collaborate. Inclusion criteria for patients will be (1) being a patient of one of the included general practices, (2) being 18 years of age or older, (3) being enrolled in a DMP for T2DM and/or for CHD and (4) being a resident of North Rhine-Westphalia. Exclusion criteria will be (1) insufficient mastery of the German language, (2) severe cognitive or physical impairments and (3) severe comorbidities. The PSG leaders will be selected from the patients by the collaborating GPs. Selection criteria for PSG leaders will be aptitude for the role of a PSG leader as assessed by the GP and the patient’s willingness to assume this role. Patients selected as a PSG leader will undergo a special training course comprising four meetings each lasting half a day. The telephone coaches will not be peers. They will be employees of the KPPP Cologne who have been trained for the study in theoretical basics such as the underlying theory of telephone-based health coaching and the technique of Motivational Interviewing. Moreover, the telephone coaches have also received practical training in conducting telephone calls via exercises with actors.

### Who will take informed consent? {26a}

The GPs who recruit the patients will inform them about the project using informational material provided by the IGKE Cologne and will obtain their informed consent. The informational material contains information about the objective of the project, the contents of the project, the inclusion and exclusion criteria, the project’s benefits and risks for the participants, data processing, data security and the participants’ rights, especially the right of withdrawing from the project at any time. Moreover, the informational material also contains addresses of the persons responsible for the project and of the agencies who are responsible for monitoring data security (see Additional File 1).

### Additional consent provisions for collection and use of participant data and biological specimens {26b}

Not applicable.

### Interventions

#### Explanation for the choice of comparators {6b}

The participants in the control group will receive their usual care together with the DMPs in which they are enrolled. This regimen will be chosen as the comparator because P-SUP is intended as a supplement to DMPs.

#### Intervention description {11a}

As mentioned above (Background and rationale {6a} section), the intervention will consist of four components:

1) Virtual and/or real meetings of PSGs

2) Personalised telephone-based health coaching for patients with low literacy and/or low patient activation

3) Personalised patient feedback

4) A browser-based web portal.

The PSGs will be organised by persons who also suffer from T2DM and/or CHD. These persons (i.e. the PSG leaders) will be trained for their task before the intervention begins for all participants. The contents of this training have been developed by experts together with patients, subjected to a pre-test with members of the target group and revised based on the results of this pre-test. The training itself will be given by specialised professionals. To maintain low threshold, these will be medical assistants, senior medical students or sports therapists who have been trained by experts. The training will be given in four meetings lasting half a day each. At the start of the training, the general objective of the intervention and the role of the PSG leaders will be elucidated. The remainder of the course will consist of two sections: one section focusing on living with chronic illness; the other on group dynamics and motivation. Among other things, methods for coping with stress, especially psychological stress in chronic illnesses, and the influence of health on personality will be discussed in the section on living with chronic illness. The aim of the section on group dynamics and motivation will be to support the PSG leaders as facilitators, mediators and motivators for the group and its individual participants. In addition, the PSG leaders will receive instructions on how emergencies can be recognised and handled. All topics will be introduced in short lectures and practised interactively in simulations. The PSG leaders will also receive a manual for follow-up and consolidation.

The PSGs will consist of 4 to 6 participants. These will be selected so that their places of residences are as close together as possible. The groups will meet weekly for the full duration of the intervention. As a rule, each meeting will last 90 min. However, the PSGs will be allowed to change the length of the meetings as they see fit. The schedule of the meetings can also be set by the PSGs. As soon as the development of the pandemic allows, the PSGs can choose between face-to-face and digital meetings. The meetings will focus on physical exercise. Individual physical exercises tailored to the abilities / possibilities of the participants will be demonstrated. The selected exercises will address coordination skills, endurance and strength development. Every second month, an external expert will visit the PSG and give a talk on a topic of relevance for people with T2DM and/or CHD. The topics will cover nutrition, medical aspects of the diseases, physical activity, motivation, further psychological aspects of the disease and general aspects of living with a chronic disease.

The telephone-based health coaching will be offered to all participants who score low on the Patient Activation Measure (PAM) [19] and/or low for health literacy (BHLS) [25] before the start of the intervention. Patients will be able to choose whether to accept the offer or not. If the offer is accepted, they will be given motivational interviewing by specially trained staff to compensate for the low levels of activation and/or health literacy. In the first phone call, patients’ intentions and previous experience with regard to physical activity and healthy nutrition will be identified. Based on these intentions and previous experience, the health coaches will then be able to individually address patients’ willingness to change their physical activity and nutritional behaviour during subsequent telephone calls. During these phone calls, various behaviour change techniques [28, 29] will be applied.

The patient feedback given to participants will be personalised and formulated for easy understanding. It will be based on the feedback reports for GPs that are currently submitted to general practices on a quarterly basis. During the intervention, the Central Research Institute of Ambulatory Health Care in Germany (Zi) will prepare these reports by translating routine GP data into personalised reports for the participants (see Additional Files 2 and 3). The Zi will send these reports to the GPs, who will forward them to the patients. This will allow participants to read about their changes (blood sugar, blood pressure values, weight and low-density cholesterol). They will then be able to discuss these changes with their GP and ask for appropriate adjustments. Participants also receiving telephone-based health coaching will be addressed by the telephone coaches about the patient feedback reports and will be given explanations about these reports.

The browser-based web portal will be accessible to all members of the intervention group through personalised access tokens. Evidence-based information on physical activity, nutrition and self-motivation will be available. Patients will be able to interact with structured behaviour change modules comprising multiple behaviour change techniques. Furthermore, the web portal will offer an online forum and a video-based exercise programme. The web portal will be password-protected.

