### Sample size {14}

The most important analysis in the evaluation addresses the effect of the intervention on the primary outcome, i.e. the number of hospital days. As mentioned above, intervention and waiting control group will be compared with regard to the change scores of hospital days. These change scores will be computed by subtracting numbers of hospital stays 1 year before intervention start from numbers of hospital stays 1 year before the intervention end. The comparison of change scores will be performed using a *t*-test for independent samples. The sample size has been determined with regard to this test. The basic demand was that the test should be able to detect an effect of size 0.2 with a significance level of 0.05 and a power of 0.8. An effect size of 0.2 is a small effect according to Cohen [39]. However, unpublished analyses of our own with numbers of hospital days indicate that the standard deviation of change scores of hospital days will be between 5 and 10. In this case, an effect size of 0.2 would correspond to differences of one to two hospital days. Even a difference of only one day would mean a substantial difference in costs.

Further conditions presupposed for determining the sample are:
Two percent of the included persons could die during the intervention period or withdraw their consent for their data to be used.There could be a dropout rate of 15% in the intervention group and 20% in the waiting control group. The reason for this assumption is that up to 50% of the sample might consist of persons who are not ensured at AOK RH or BARMER. For these persons, the numbers of hospital days will not be provided directly by the health insurance companies. Instead, the patients will have to request the data from their health insurance companies and then transfer them to the project team. Several patients will not do this, with patients in the waiting control group being more likely not to do this. Within this sub-sample, a dropout rate of 30% in the intervention group and 40% in the waiting control group seems realistic. This would correspond to dropout rates of 15% and 20% in the total sample.The allocation ratio of intervention to control is 6:7.The sample size should be divisible by 13 because of the allocation ratio.

All these considerations imply a sample size of 1001.

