## Statistical methods

### Statistical methods for primary and secondary outcomes {20a}

To test the effect of the intervention on the primary outcome (i.e. on number of hospital days), the number of hospital days directly before the start of the intervention and the number of hospital days directly before the end of the intervention will be determined. The differences between these numbers will be computed, and the intervention and control groups will be compared with regard to these differences using a *t*-test for independent samples.

As outlined above (see the ‘Objectives {7}’ section), the effect of the intervention on the number of hospital days is assumed to be mediated by several different variables. Each step of the mediation will take some time. For this reason, there may well be no effect on the primary outcome although effects on the preceding variables are already identifiable. Such a pattern of results would also indicate an effect of the intervention. Consequently, if there is no statistically significant effect for the primary outcome, the pattern for the secondary outcomes will be applied in order to decide the effectiveness of the intervention. For this purpose, all secondary variables will be z-transformed and poled so that higher numbers mean better outcomes in all variables. All variables transformed in this way will be subjected to a two-factorial analysis of variance with the variables as a within-subjects factor and the study condition as a between-subjects factor. The intervention will be judged as effective if there is a statistically significant effect in favour of the intervention group. To judge whether the secondary outcomes actually determine the primary outcome, the relationships between secondary outcomes and primary outcome will be analysed using a cross-lagged panel approach with data from baseline and end surveys as predictors and the number of hospital days for the corresponding time intervals as criteria.

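### Only the intervention arm is treated in peer groups, yet the tests and the sample size assume independent participants; if the groups induce correlation, the standard error is too small and the power overstated

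*Protocol article*

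**What the plan says.** **Delivery.** Section Intervention description {11a} of the protocol article states: "The PSGs will consist of 4 to 6 participants" and "The groups will meet weekly for the full duration of the intervention". The Abstract gives the duration as 18 months. Each group has a trained patient leader. Members are chosen to live near each other, and each group may set its own schedule and meeting length and, once the pandemic permits, choose between digital and face-to-face meetings. Under Criteria for discontinuing or modifying allocated interventions {11b}, activities are agreed with the members. Controls remain on usual care over the same period.

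**Analysis.** Under Statistical methods {20a}, each patient's change in hospital days is taken and the two arms are "compared with regard to these differences using a *t*-test for independent samples". If that test is not significant, effectiveness is decided by an analysis of variance on the standardised secondary outcomes, with outcome variable as the within-subject factor and study condition as the only between-subject factor.

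**Sample size.** Section Sample size {14} says of the t-test: "The sample size has been determined with regard to this test". The requirement is that "the test should be able to detect an effect of size 0.2 with a significance level of 0.05 and a power of 0.8". The further conditions listed are 2% death or withdrawal of consent, dropout of 15% (intervention) and 20% (control), the 6:7 ratio and divisibility by 13. The result is 1001. Neither an ICC nor a design effect is mentioned.

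**The concern.** This is an individually randomised trial with clustering by treatment group in one arm. Members of a group share a leader, a meeting format, a set of activities and each other's advice, so the dose and quality of what they receive vary by group. Controls have no such grouping during the comparison period. An independent-samples test counts every intervention patient as a separate piece of information. If the groups make their members' outcomes alike, that overstates the information in that arm.

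Two things are at stake. The first is a test that rejects more often than its nominal 5%. This matters most for the fallback analysis, because a significant result there is enough for the programme to be judged effective, and several of its outcomes (physical activity, loneliness, self-efficacy) are ones that group contact is meant to change. The second is power: 1001 has little slack, and the Discussion already warns that it may not be reached.

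**Working it through.** **Inputs.** From Sample size {14}: d = 0.2, alpha = 0.05, power 0.80, ratio 6:7, 2% death or withdrawal, dropout 15% and 20%, N = 1001. From Intervention description {11a}: groups of 4 to 6, midpoint 5. *Assumptions:* a two-sided test (sidedness is not stated) and an ICC of the change score from 0 to 0.10 (no value is given).

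**Step 1: reproduce the plan's figure.** 1001 splits 462 : 539.

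- Intervention evaluable: 462 × 0.98 × 0.85 = 384.8
- Control evaluable: 539 × 0.98 × 0.80 = 422.6
- Variance in SD units: 1/384.8 + 1/422.6 = 0.0025984 + 0.0023664 = 0.0049649, so SE = 0.07046
- Power = Φ(0.2/0.07046 − 1.960) = Φ(0.878) = 81.0%

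The smallest multiple of 13 that reaches 80% is 988, so 1001 is reproduced to within 1.3%. It contains about one percentage point of spare power and no allowance for clustering.

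**Step 2: co-members per evaluable patient.** In a group of 5, a patient has 4 co-members. Because the 384.8 is net of losses, the co-members must be too: 4 × 0.98 × 0.85 = 3.33.

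**Step 3: cluster the intervention arm only.**

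- Design effect: DE = 1 + 3.33 × ICC
- True variance: V = DE/384.8 + 1/422.6
- Actual type I error of the planned test: 2 × [1 − Φ(1.960 / √(V/0.0049649))]
- Power of a test using the correct SE: Φ(0.2/√V − 1.960)

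| Assumed ICC | DE | V | True SE / planned SE | Type I error | Power at N = 1001 |
|---|---|---|---|---|---|
| 0 | 1.00 | 0.0049649 | 1.000 | 5.0% | 81.0% |
| 0.01 | 1.03 | 0.0050515 | 1.009 | 5.2% | 80.3% |
| 0.02 | 1.07 | 0.0051380 | 1.017 | 5.4% | 79.7% |
| 0.05 | 1.17 | 0.0053978 | 1.043 | 6.0% | 77.7% |
| 0.10 | 1.33 | 0.0058307 | 1.084 | 7.1% | 74.5% |

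**Step 4: where the 80% is lost.** 80% power needs 0.2/√V = 1.960 + 0.842 = 2.802, so V = 0.0050963. Then DE = (0.0050963 − 0.0023664)/0.0025984 = 1.0506, and ICC = 0.0506/3.33 = 0.015. For groups of 4 (3 × 0.833 = 2.50 co-members) the limit is 0.0506/2.50 = 0.020. For groups of 6 (5 × 0.833 = 4.17) it is 0.0506/4.17 = 0.012.

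No corresponding figure is computed for the fallback analysis of variance. That would need group-level correlations and correlations between outcomes that the protocol does not give.

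**The case against.** The strongest counter-argument is that the groups are small and the ICC is unknown. At an ICC of 0.01 the trial still has 80.3% power and the type I error is 5.2%; at 0.02 the departures are of no practical weight. Nothing in the protocol supports 0.05 or 0.10 for change in insurer-recorded hospital days, the outcome on which 1001 is built. Telephone coaching, feedback reports and the web portal reach patients as individuals, which should dilute any group effect. All of this stands, and it limits the size of the point. It does not remove it: the direction is the same for any positive group-induced ICC, and the protocol itself names the test and sizes the trial for it, so the choice was not left open for an analysis plan.

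Three stronger readings are tempting and are not supported.

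- *The planned error bars are certainly too narrow.* This follows only if the groups induce positive correlation. That is plausible, but the documents do not establish it.
- *The groups have fixed membership.* The protocol says that groups meet throughout, not that membership is constant. Patients may stop when they like ({11b}) and may use components or not ({20c}).
- *Living close together is itself a source of one-arm clustering.* Randomisation is individual and stratified by the six recruitment areas ({16a}), so controls come from the same areas. Only correlation created by the groups belongs in the design effect. A model that codes every control as a singleton may attribute some pre-existing local similarity to the groups, and this should be kept in mind when its ICC is read.

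**Conclusion.** The point holds in conditional form. One arm is treated in groups, and neither test nor the sample size allows for it. If the groups induce a positive ICC, the planned standard error is too small and the power is overstated. Under the stated assumptions (groups of 5, losses as planned, two-sided 5%), the standard error is short by about 1% at an ICC of 0.01 and 8% at 0.10. Type I error runs from 5.2% to 7.1% and power from 80.3% to 74.5%; the 80% target fails above an ICC of about 0.015. For hospital days the effect may be small. For loneliness, activity and self-efficacy it could be larger, and those outcomes feed the fallback verdict, but that remains a judgement and not a calculated result. The analysis should be corrected; the design need not change.

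**What to change.** 1. In {20a}, analyse the primary and all secondary outcomes, including the fallback test, with a partially nested mixed model: a random peer-group effect in the intervention arm by assigned group, each control as a singleton, and arm-specific residual variance. Standard errors clustered by peer group, with controls as singletons, are an acceptable alternative.
2. In {14}, replace the single power figure with power over a stated range of ICCs, applying the design effect to the intervention arm only and using evaluable co-members.
3. Report the estimated ICC for each outcome.

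**Cost.** Intervals become slightly wider and the stated power slightly lower; no extra patients or visits are required. There is one practical requirement. Section {11c} provides for attendance to be documented by the group leaders, which does not guarantee that the assigned group is known for patients who never attend. Assigned group must be recorded for every intervention participant and carried, under the study identification number, through the pseudonymisation described in Confidentiality {27} into the analysis file.
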